### Interim analyses {21b}

A blinded restricted re-evaluation of the standard deviation assumed for the sample size calculation will be performed after an information rate (IR) of 40% is reached, meaning that 40% of the patients have completed the 90-day follow-up assessment of the primary outcome CCI. The estimation of the standard deviation will be performed on the combined set of patients of the intervention and control group, and therefore unblinding is not necessary. If the standard deviation at interim is larger than anticipated, an increase of the sample size will be discussed. No reduction of the sample size is planned. No statistical reasons for stopping the trial at interim have been specified. The trial may be stopped for other reasons, including slower recruitment than anticipated.

### Methods for additional analyses (e.g. subgroup analyses) {20b}

This is reported in the statistical analysis plan.

### Methods in analysis to handle protocol non-adherence and any statistical methods to handle missing data {20c}

Participants whose surgery is cancelled or takes place more than 4 months after randomization, do not attend for surgery or withdraw their consent before surgery or during the hospital stay will not be included in the intention to treat population. To ensure an adequate number of participants in the study, participants without surgery within 4 months after randomization and participants who withdraw their consent before surgery or during the hospital stay will be replaced by recruitment of new subjects. Patients included in the study but with the rescheduled date of surgery and <4 weeks between randomisation and surgery will not be excluded. Other missing data and postoperative loss of follow-up after three months will be addressed with multiple imputation in the primary analysis.

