### Sample size {14}

Based on a previous Cochrane review with meta-analysis [7], it is assumed that preoperative smoking cessation decreases the binary outcome of postoperative complications (yes or no) with a relative risk of 0.42. The mean postoperative CCI as a continuous measure in a retrospective chart review in a cohort without smoking cessation at the hospital of Lucerne was 13 and we therefore assume a CCI of 5.5 in the intervention group. The assumed standard deviation for the sample size calculation was 20. With anticipated 80% power, a two-sided significance level α of 5%, a sample size of 226 patients is planned. With an additional 10% dropout, our aim is to enrol 251 patients.

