## Statistical methods

### Statistical methods for primary and secondary outcomes {20a}

A detailed statistical analysis plan has been written up as an Additional file 3 to the submission. According to the intention to treat (ITT) principle, patients will be analysed according to the treatment group they have been assigned to by randomisation. The full analysis set (FAS) consists of the patients randomized and receiving surgery within 4 months after randomization. The FAS will be the primary population for the efficacy analysis.

Primary outcome CCI will be addressed with a multiple linear model, including a randomized treatment group, and the minimization variables (age ≤60 or >60 and intermediate or high-risk surgery) as independent variables. If after normality check with a qq-plot the residual distribution is skewed a transformation of the CCI may become necessary. To evaluate the between-group difference in CCI of the smoking cessation intervention versus the control group, adjusted for the above-defined confounders, the estimated between-group difference with 95% confidence interval and corresponding p-value will be reported. For the secondary outcomes, linear, logistic, or Poisson regression models including the randomized treatment group as an independent variable, will be used to estimate the treatment effect between treatment groups. Normality will again be checked using qq-plot and, if necessary, appropriate transformations of the dependent variable will be made.

For the comparison of readmission rates between the treatment groups, the date of discharge from the hospital after surgery will be chosen as the starting observational time point and a Poisson model, considering readmissions collectively, will be fitted to estimate the incidence rates of readmission per treatment group within 90 days after discharge. The result will be reported as a rate ratio (RR) and the Poisson model will be corrected for overdispersion if necessary.

To estimate the hazard ratio for the first readmission, again with starting time point at discharge, a Cox-model will be used.

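### Two protocol sections define the primary population differently, and both drop patients operated after 4 months, whose 90-day CCI can still be determined

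*Protocol article*

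**What the plan says.** Statistical methods for primary and secondary outcomes {20a} commits to analysis by assigned group and then defines the primary efficacy population: "The full analysis set (FAS) consists of the patients randomized and receiving surgery within 4 months after randomization". Consent withdrawal does not appear in that definition.

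Section {20c}, on non-adherence and missing data, lists those left out of the ITT population: patients whose operation is cancelled or later than 4 months, patients who do not attend, and patients who "withdraw their consent before surgery or during the hospital stay will not be included in the intention to treat population". Those without an operation within 4 months are replaced, and likewise "participants who withdraw their consent before surgery or during the hospital stay will be replaced by recruitment of new subjects". Patients whose rescheduled operation falls less than 4 weeks after randomisation are kept. Multiple imputation is reserved for other missing data and for loss to follow-up after three months.

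Outcomes {12} sets the primary endpoint as the CCI within 90 days of surgery, taken from health records and including complications treated at other institutions. Sample size {14} plans 226 patients and adds: "With an additional 10% dropout, our aim is to enrol 251 patients".

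**The concern.** There are three problems, in order of weight.

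1. **Withdrawal in hospital.** Section {20c} names this separately from withdrawal before surgery, so the natural reading is withdrawal after the operation, when complications that count towards the CCI may already have occurred. If withdrawal is related to those complications, removing the patient selects on the endpoint. {20a} keeps this patient and {20c} removes and replaces the same patient, so two analysts following the protocol could build different primary datasets.

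2. **Surgery after 4 months.** Both sections exclude these patients although their endpoint can be determined. Delay happens after randomisation. Only one arm has a preoperative counselling programme, and participants know which arm they are in, so timing and willingness to continue could differ by arm.

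3. **Replacement alongside inflation.** The sample is already enlarged for dropout, and {20c} also replaces excluded patients. The article does not say which losses the 10% covers.

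At stake is whether the primary comparison rests on the groups that randomisation formed. Recruiting new patients restores the count but not that comparability.

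**Working it through.** **The plan's own figure.** Inputs from Sample size {14}: control mean CCI 13 and intervention mean 5.5 ("at the hospital of Lucerne was 13 and we therefore assume a CCI of 5.5 in the intervention group"; 13 × 0.42 = 5.46), so the difference is 7.5; SD 20; two-sided α 0.05; power 80%; allocation 1:1. A two-sample t-test needs 112.6, so 113 per arm and 226 in total, as stated. The normal approximation gives 112 per arm, 224 in total. For dropout, 226 / 0.90 = 251.1, stated as 251. The arithmetic is sound; the issue lies in the population.

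**The two sections side by side.**

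| Patient | Set in {20a} | ITT population in {20c} | CCI within 90 days of surgery |
|---|---|---|---|
| Never operated | out | out, replaced | does not exist |
| Withdraws before surgery | no consent rule; out if not operated | out, replaced | not available |
| Operated within 4 months, withdraws in hospital | **in** | **out, replaced** | partly observed |
| Operated after 4 months | out | out, replaced | can be determined |
| Operated under 4 weeks after randomisation | in | in | can be determined |

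The third row is the contradiction. The fourth is an exclusion that the endpoint definition does not require.

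**Illustration 1 (assumed): withdrawals in one arm only, replaced by average patients.** Suppose k patients with CCI 50 leave an arm of 113 whose mean is 13. The arm mean falls by k × (50 − 13) / 113.

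- k = 3: 111 / 113 = 0.98 points, 13% of 7.5.
- k = 5: 185 / 113 = 1.64 points, 22% of 7.5.

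If these are controls, the control mean falls and the observed benefit **shrinks**. If they are intervention patients and that arm's mean is 5.5, the shifts are 3 × 44.5 / 113 = 1.18 and 5 × 44.5 / 113 = 1.97 points, and the observed benefit **grows**.

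**Illustration 2 (assumed): type I error when there is no true effect.** A share f is excluded in one arm only, and the excluded patients' mean CCI lies a gap g above the arm mean. Bias = f × g / (1 − f); SE = 20 × √(2/113) = 2.66.

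| f | Bias for g = 10 to 30 | Type I error |
|---|---|---|
| 2% | 0.20 to 0.61 | 0.051 to 0.056 |
| 5% | 0.53 to 1.58 | 0.055 to 0.091 |
| 10% | 1.11 to 3.33 | 0.070 to 0.240 |

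The article gives neither f nor g. Exclusions that are balanced between arms and unrelated to outcome would cause no bias.

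**Overlap of allowance and replacement.** If all the losses behind the 10% were also replaced, about 251 patients would be analysed, not 226. At the stated inputs power is then about 84% instead of 80%. Neither power nor validity suffers from the overlap itself.

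**The case against.** The strongest reply is that {20a} is the section that names the primary population, and it has no consent rule. On that reading an operated patient who withdraws in hospital stays in the primary analysis, and {20c} is loose wording. This partly stands. A reader might infer that the primary comparison definitely loses these patients, and the article does not settle that. What remains is a contradiction between two operative sections. The incorrect ITT label belongs to {20c} alone, since {20a} calls its set the full analysis set.

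A second reply is that some post-randomisation exclusion is unavoidable, because a CCI counted from surgery does not exist without surgery. That stands for patients never operated. It does not cover late surgery or withdrawal after the operation.

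A third is that the mechanisms are conjecture: nothing says operations are moved to suit the programme, or that withdrawal follows complications. This also stands, and limits the point to lost protection.

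Two further inferences should be resisted. A reader might take 10% of 251, about 25 patients, as the number affected, but that is a general dropout allowance which no section ties to late surgery or in-hospital withdrawal. A reader might also say that replacement leaves the sample size undefined, yet 226 and 251 are both stated; only the losses covered by the 10% are unclear.

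**Conclusion.** The point holds as an inconsistency in the primary population plus an unnecessary exclusion, and it should be corrected before analysis. {20a} and {20c} disagree on in-hospital withdrawal, and both remove late-surgery patients whose endpoint can be determined. The comparison loses some of the protection of randomisation, and replacement cannot give it back.

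Bias is not shown. Under the assumed scenarios the effect runs from negligible (0.2 points, type I error 0.051) to serious (3.3 points, type I error 0.24). The upper end needs 10% exclusion confined to one arm and a 30-point gap. Direction depends on the arm that loses patients: loss of high-CCI controls works against the superiority claim, and loss of high-CCI intervention patients works for it. The unseen analysis plan may clarify the set, but the protocol text would still need to be brought into line.

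**What to change.** Reconcile {20a} and {20c} around one definition:

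- **Primary set:** all randomised patients who undergo surgery, whenever it takes place, analysed in the assigned arm, with the CCI over 90 days from surgery.
- **Withdrawal after surgery:** the patient stays in. Use complications recorded up to withdrawal, as consent permits, and extend the multiple imputation already planned to the remainder.
- **Left out:** only patients never operated or withdrawn before surgery. Call the set modified ITT and report numbers and reasons by arm.
- **Sensitivity set:** surgery within 4 months of randomisation.
- **Sample size:** state which losses the 10% covers and which are replaced, so that the two do not overlap.

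The cost is wording in the protocol and analysis plan. Complications are already read from health records, so no new data system is needed.

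The downside is that a few late-surgery patients, with a possibly diluted effect, enter the primary analysis. As a pessimistic assumption, let a share of 251 analysed patients gain no benefit at all. With 5%, the effect is 7.5 × 0.95 = 7.125, power is about 81%, and 248 patients give 80%. With 10%, the effect is 6.75, power is about 76%, and 276 would be needed.

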### Plans to give access to the full protocol, participant level-data and statistical code {31c}

The statistical analysis plan was submitted as Additional file 3 to the submission. The statistical code will be published as supplementary material, together with the main results of the study.

## Oversight and monitoring

### Composition of the coordinating centre and trial steering committee {5d}

The principal investigator will meet every Tuesday morning with the clinical nurse, and advanced nurse practitioner to discuss day-to-day support for the trial. The Trial Steering Committee consists of the principal investigator and the statistical head will meet regularly every 3 months.

### Composition of the data monitoring committee, its role and reporting structure {21a}

The data monitoring committee (DMC) will reassess the data in a blinded fashion as described to check the variability to reassess the sample size calculation.

### Adverse event reporting and harms {22}

An *adverse event (AE)* is any untoward medical occurrence in a patient or a clinical investigation subject which does not necessarily have a causal relationship with the trial procedure. An AE can therefore be any unfavourable or unintended finding, symptom, or disease temporally associated with a trial procedure, whether or not related to it.

A *serious adverse event (SAE)* (ClinO, Art. 63 [24]) is any untoward medical occurrence thatResults in death or is life-threatening,Requires in-patient hospitalisation or prolongation of existing hospitalisation,Results in persistent or significant disability or incapacity, orCauses a congenital anomaly or birth defect

As the causal relationship between the events and the intervention can be ruled out, any event assessment regarding causality and severity will not be performed.

Both Investigator and Sponsor-Investigator make a severity assessment of the event as mild, moderate or severe. Mild means the complication is tolerable, moderate means it interferes with daily activities and severe means it renders daily activities impossible.

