### Intervention description {11a}

The study intervention consists of an interview by a Tobacco Treatment Specialist (TTS) 4 weeks before surgery with individual counselling and offered nicotine substitution. All TTS have > 15 years of experience and underwent a postgraduation course for counselling smoking cessation. The intervention meeting is based on the Chronic Care Model (CCM) [11, 12] to improve the quality of ambulatory care through six interrelated system changes [13]: self-management support, decision support, delivery system design, clinical information systems, health care organisation, and community resources. In line with the CCM, the intervention will include the following elements adapted from Haas et al. randomized clinical trial [14] and are described in the treatment plan. In brief, the intervention includes:Informative content about advantages of smoking cessation [15] using information leaflets along with decision supportScheduling service for a motivational interview by a TSS in the office to provide educational and motivational content, explain the magnitude and profile of nicotine dependence and implement a treatment plan [16]For participants willing to quit smoking a preoperative quit day will be scheduled after the first intervention meeting 2–3 weeks before surgery. Time of a preoperative quit day may vary between patients, since our smoking intervention focuses on as early quit attempts as possible. Therefore, there will be a variety in patients with one or more quit attempts, with or without success, and patients who quit smoking in the postoperative period, only.Patients will be encouraged by a TSS to use nicotine replacement with patches/gums/pills at their own discretion. For smokers of 20 cigarettes per day or more, a 4-week supply of 21mg/day, 2-week supply of 14 mg/day and a 2-week supply of 7 mg/days patches will be provided. Patients who smoke between 10 and 20 cigarettes per day will receive a 4-week supply of 14 mg/day and a 4-week supply of 7 mg/day. Smokers of <10 cigarettes per day will be supplied with a 4- to 8-week supply of 7-mg/day patches. Bupropion or Varenicillin will be provided on an individual basis (all costs are covered by the patient’s insurance).

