#### Reporting of SAEs (see ClinO, Art. 63)

The primary outcome and events on which the sample size is based represent postoperative complications which include SAEs. All SAEs within 90 days after surgery will be documented and analysed in this trial. As the origin of the SAEs is not intervention related, the SAEs are not actively reported to the EC in the applicable time limit of 15 days but are summarised in the annual safety report (ASR).

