## Discussion

The dedicated smoking cessation intervention is expected to cause sustained abstinence from smoking in a large percentage of the patients. The hypothesis is that the preoperative smoking cessation program improves outcomes in smokers undergoing surgery. The study will reveal if the expectations on successful smoking cessation rates are reasonable.

To date, only two RCTs have investigated the effects of an intensive preoperative smoking cessation program on postoperative complications [5, 6]. Even though the preoperative period is considered as a window of opportunity for cessation counselling randomized controlled evidence regarding its efficacy is still lacking. A systematic Cochrane Review showed evidence for increased short-term smoking abstinence in patients undergoing preoperative cessation counselling, whereas the effects on long-term abstinence and postoperative morbidity remained unclear [7].

In contrast to these previous studies, postoperative morbidity will be assessed using the CCI over a 90-day period. The CCI has been proven to be a strong endpoint, as it reflects the overall burden of the postoperative course in a single patient and thus allows for smaller sample sizes compared with traditional morbidity endpoints.

In line with most RCTs regarding preoperative cessation counselling, it is likely that the major limitations of our trial will be the relatively short preoperative period and the intensity of cessation counselling. To overcome these barriers our trial will only enrol patients who are scheduled for surgery with a preoperative period of more than one month and an intensive cessation program consisting of weekly behavioural support and pharmacotherapy will be implemented in as many patients as possible.

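### The safety section contradicts itself on severity, rules out causality in advance for a programme that includes medicines, and states no serious-event window before surgery or for patients not operated on

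*Protocol article*

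**What the plan says.** All references are to the protocol article.

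- **Severity and causality.** Adverse event reporting and harms {22} states "As the causal relationship between the events and the intervention can be ruled out, any event assessment regarding causality and severity will not be performed". The paragraph after it states "Both Investigator and Sponsor-Investigator make a severity assessment of the event as mild, moderate or severe" and defines the three grades.
- **Reporting.** Reporting of SAEs sets aside the 15-day limit for notifying the ethics committee: "As the origin of the SAEs is not intervention related, the SAEs are not actively reported to the EC in the applicable time limit of" (the sentence goes on to name that limit). The events go into the annual safety report instead.
- **Window.** The same section says "All SAEs within 90 days after surgery will be documented and analysed in this trial". It also says that the complications forming the primary outcome include SAEs.
- **Medicines.** Intervention description {11a} describes "an interview by a Tobacco Treatment Specialist (TTS) 4 weeks before surgery with individual counselling and offered nicotine substitution". It continues "Patients will be encouraged by a TSS to use nicotine replacement with patches/gums/pills at their own discretion", sets out patch supplies, and adds "Bupropion or Varenicillin will be provided on an individual basis". The Discussion describes "an intensive cessation program consisting of weekly behavioural support and pharmacotherapy will be implemented in as many patients as possible".
- **Patients not operated on.** Section {20c} leaves out of the intention-to-treat population those whose surgery is cancelled or falls more than 4 months after randomisation, those who do not attend, and those who withdraw consent before surgery or during the hospital stay. Those without surgery within 4 months and those who withdraw consent are replaced.

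**The concern.** There are three linked problems.

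1. Staff cannot follow both severity sentences.
2. Whether an intervention containing medicines can cause an adverse event is a question for data and case assessment. Here the answer is fixed beforehand and then used to justify a reporting rule.
3. The stated collection window opens at surgery, but the intervention opens about 4 weeks earlier. A serious event before surgery has no stated place in the trial's safety data. If the event stops the operation, the patient also leaves the analysis population and is replaced.

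At stake is the comparison of harms between arms. A trial that reports benefit on postoperative complications should be able to show what happened to everyone from the moment they were assigned to the programme or to advice only.

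**Working it through.** The plan states no figure on this point, so the check is mainly a comparison of sections.

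**Step 1: severity.** One sentence in {22} covers causality and severity together and says neither will be assessed. The next paragraph assigns severity grading to two roles. Nothing separates the two by event type, period or arm, so they cannot both apply.

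**Step 2: causality.** Two other parts of the document conflict with ruling it out.
- {11a} offers nicotine replacement, supplies patches, and provides bupropion or varenicline (spelled differently in the text) case by case. The Discussion counts pharmacotherapy as part of the programme.
- Objectives {7} and Trial design {8} set up a superiority trial of whether the programme changes postoperative complications, and Sample size {14} uses a two-sided test. Since those complications include SAEs, the trial tests for a causal effect on events that the harms section says cannot be causally related.

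**Step 3: when collection is stated to start.**

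| Event | Timing | Source |
|---|---|---|
| Intervention interview, nicotine substitution offered | 4 weeks before surgery | {11a} |
| Quit day | 2–3 weeks before surgery | {11a} |
| Latest surgery for the full analysis set | 4 months after randomisation | {20a} |
| SAE documentation | the 90 days after surgery | Reporting of SAEs |

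No section states an SAE window between randomisation and surgery. For a patient who is never operated on, a window counted from surgery does not exist.

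**Step 4: does another section fill the gap?**
- {23} plans two unblinded safety analyses, after 50 and 100 patients, but of postoperative complications expressed as the CCI.
- {21a} gives the data monitoring committee a blinded look at variability for the sample size.
- {20c} identifies patients with cancelled or late surgery, but only to exclude or replace them.

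None of these covers preoperative events.

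**Step 5: how much medicine exposure precedes surgery?** The patch supply in {11a} totals 4 + 2 + 2 = 8 weeks for the heaviest smokers, 4 + 4 = 8 weeks for the middle group, and 4 to 8 weeks for the lightest. The document does not give the patch start date, so it is assumed here to be either the quit day or the 4-week interview, with surgery on schedule.

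| Assumed start | Share of 8-week supply before surgery | Share of 4-week supply before surgery |
|---|---|---|
| 2 weeks before surgery | 2/8 = 25% | 2/4 = 50% |
| 3 weeks before surgery | 3/8 = 37.5% | 3/4 = 75% |
| 4 weeks before surgery | 4/8 = 50% | 4/4 = 100% |

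So the period without a stated window is the first part of the exposure. For an 8-week supply it is at most half.

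**The case against.** The strongest reply is that this is a journal article condensing a fuller protocol. The text does not say that SAEs are documented *only* after surgery, the adverse event definition in {22} has no postoperative limit, and the start of collection may be fixed in the full document. That stands as a limit on wording: the supportable statement is that no preoperative window is stated. It does not remove the severity contradiction or the advance statement on causality, both of which are in the text as published.

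Several stronger readings are tempting and are not supported.

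- *The main exposure period is unobserved.* On the planned schedule, at least half of an 8-week patch supply falls after surgery, inside the 90-day window. Expressing the time from randomisation to surgery as a share of total follow-up would not help either: that is calendar time, and time before the interview is not exposure to the programme.
- *Harms cannot be detected.* Routine entries exist in the electronic chart ({18a}), and cancelled or late surgery is an identified category that could be counted by arm. What is missing is stated trial documentation and comparison.
- *The 10% dropout allowance caps the number of patients without surgery.* It does not, because they are replaced, and the document gives no cancellation rate.
- *Medicine exposure is confined to one arm.* Controls may obtain cessation aids themselves ({6b}), which is a reason to assess both arms alike.

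It is also true that the primary endpoint uses Clavien–Dindo grades ({12}), not the mild, moderate and severe scale, so the severity contradiction does not alter its grading.

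**Conclusion.** The point holds in three parts.

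1. The contradiction on severity is explicit and needs no assumption.
2. The claim that causality is ruled out conflicts with the medicines in the intervention and with the trial's own hypothesis, and the 15-day reporting exemption rests on it.
3. The only SAE window stated begins at surgery. About 4 weeks of intervention on the planned schedule, a randomisation-to-surgery interval of up to 4 months within the full analysis set, and all follow-up of patients not operated on have no stated safety documentation.

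The third part assumes that the fuller protocol does not set an earlier start; the first two do not depend on that. The number of events affected cannot be estimated, because the document gives no preoperative event rate and no cancellation rate. The consequence is an incomplete comparison of harms. No error in the grading or model of the primary endpoint has been shown on this point.

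**What to change.** - **Severity:** reconcile the two sentences in {22} so that the text says once whether severity is assessed, by whom and for which events.
- **Causality:** delete the statements that a causal link is ruled out and that SAEs are not intervention related. Reconcile the reporting rule built on them with {11a}.
- **Window:** document SAEs from randomisation to 90 days after surgery in both arms. Include patients who are not operated on, over a stated equivalent period and as far as their consent allows.
- **Relatedness:** assess it by the same rule in both arms. Recording it only for users of the medicines would make ascertainment uneven.
- **Reporting of results:** tabulate SAEs, and cancelled or delayed surgery, by arm for all randomised patients, separately from the full analysis set.
- **Access:** state who may see arm-level safety data while the trial runs. Reconcile this with {21a}, which gives the committee a blinded role, and {23}, which plans unblinded safety analyses.

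The cost is a wording amendment and a modest amount of extra chart review, since trial data are already collected in the hospital's electronic chart. No dose or treatment rule is affected.
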